#### Secondary outcomes

1. Determine the effect of HRSLE on: 1) endurance time, ventilatory response, perceived dyspnea and leg fatigue during submaximal cycle test; 2) maximal strength and muscular endurance during isokinetic tests; and 3) self reported dyspnea, self-efficacy, anxiety and depression.

2. Determine the relationship between: 1) changes in self reported dyspnea, self-efficacy, anxiety and depression; and 2) changes in exercise capacity

3. Identify if there are any sex-related differences in exercise training effects.

4. Determine if this exercise regimen is feasible and safe in stage II-IV COPD patients.

5. Develop a strategy to minimize attempts needed to determine a multiple repetition resistance using elastic bands.

6. Develop a strategy to optimize resistance for each involved movement within an exercise regimen.

7. Investigate the relationship between muscle fatigue and dyspnea in the different exercise tests.

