##### Initial load

To be able to enhance the accuracy of each individual patient receiving adequate initial resistance for each separate exercise we aim to use a three-step approach:

1 A pilot study was performed on 30 healthy individuals, in a similar age group as the patients within this study. The results of the pilot study showed a strong relationship between elastic resistance maximal voluntary contraction (MVC) and isokinetic peak value during shoulder flexion with no significant difference in weight (kg). Based on this pilot study, the peak value obtained from the isokinetic tests at baseline within the present study will be used to determine MVC (that is, 1 RM) using elastic resistance [36]. Fifty-five per cent of the isokinetic peak value will be used as 25 RM as recommended by Page and Ellenbecker [36]. However, the choice of standardizing the training load from a MVC using elastic resistance has been questioned. Therefore, a goal-based 25 RM test will also be performed [37]. The number of attempts needed to reach 25 RM will be recorded.

2 Based on a literature search the following percentage strength relationships between involved muscles for COPD patients during the movements that are involved in this HRSLE were identified (described as weight at end position if knee extension is seen as maximal): knee extension (100%), chest press (85%), leg curl (65%), elbow flexion (50%), latissimus row (35%), shoulder flexion (30%). For example, if 10 kg is considered 55% of 1 RM for knee extension, 3 kg would be considered 55% of 1 RM for shoulder flexion.

3 According to the strength relationship between involved muscles and information obtained regarding the weight properties of elastic resistance at a given length (Thera-Band values provided by the manufacturer; The Hygenic Corporation), the distance from insertion for each exercise using elastic resistance is determined (see Additional file 2).

By using different starting positions for each exercise (that is, the elastic tubing is stretched to different lengths resulting in different resistances at every position) we hope to be able to optimize the resistance for the involved muscle during each separate exercise. Two elastic resistance bands (the same color) will be needed (one fastened at the lowest level of the wall bar and the other fastened at the highest level) for all elastic exercises within the HRSLE.

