### Sample size

A sample size of 17 in each group (intervention, control) will be required to obtain the power to detect a significant difference in lower limb local muscular endurance capacity measured by the 6-MWT [53]. The sample size calculation was made with the following assumptions: a relevant mean difference of 50 meters walked in 6 minutes with a standard deviation (SD) of 52, α = 0.05, β = 0.20 (80% power); and a two-tailed test of significance, based on a study by Costi and colleagues [54] (a RCT published in 2009 on unsupported training in patients with COPD). For QoL, the sample size calculation was made with these assumptions: a relevant mean difference of 1 unit (SD 1.07) on the Swedish version of the CRQ, α = 0.05, β = 0.20 (80% power); and a two-tailed test of significance, data based on CRQ values obtained in the study by Lacasse and colleagues [75] gave 17 patients in each group. Multicenter trials involve a correlation in data - subjects from the same center are likely to be more similar than subjects from other centers. Because such a correlation potentially affects the power of the data within the trial, the sample size needs to be adjusted, often increased, to account for the design of the study - in other words, the design effect [76]. Several considerations have been made to minimize the effect of using different centers: the same inclusion criteria for participants at all locations; specified and similar inclusion criteria for physiotherapists at all locations; standardized training for all physiotherapists to uniformly deliver the intervention; all aspects of the intervention regimen are standardized; a standardized exercise protocol will be given to both physiotherapists leading interventions and participants; physiotherapists give informed consent to follow the standardized instructions regarding the standardized patient education material; and exercise protocol and primary outcome measures are measured by the same (blinded) outcome assessor at all centers during pre- and post-tests. In addition, in an individually randomized trial, stratified for centers, the design effect is estimated to be < 1 which involves a gain in power, allowing a reduction in sample size rather than an increase [76,77]. With regard to the design of the study and the considerations taken to minimize the effect of using different centers, no adjustment of sample size will be made due to design effect. Nevertheless, the sample size is adjusted for potential drop-outs. We expect a drop-out rate of 20% based on a previous systematic review [78]. We aim to recruit five additional patients to each group, resulting in a total number of 44 patients, 22 in each group (17/0.8 = 21.3 ≈ 22) with moderate to very severe COPD. The total study group will consist of an equal number of males and females.

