### Statistics

The analysis of primary and secondary outcome measurements will include all randomized patients. To be able to use all patient data, the mixed models approach will be adopted with individuals at level one and center at level two. The analysis will demonstrate any improvements at follow-up, comparing the intervention and control group. In linear mixed models the variable group is considered main, controlling for baseline value, center and gender. To judge the quality of the model we will analyze the residuals. A difference at the *P* < 0.05 level will be considered significant in all outcome measures and analyses. For each outcome the results will be reported as a summary of the outcome in each group presented as mean and SD, together with effect size. For treatment effect, 95% confidence intervals (CI) and *P* values will be presented. For each group, information about the number of participants included in each separate analysis and whether theses analyses were by original assigned groups will be given. Correlation between changes in physical variables and changes in health variables will be measured by Pearson correlation. A pre-specified subgroup analysis of participants randomized to the intervention group will be performed to investigate differences in BORG CR10 rating between elastic resistance exercises to evaluate the strength relationship between involved muscles/movements. Our research group has previously found relatively lower thigh muscle strength in female patients with COPD compared to male patients with COPD and healthy controls [32]. In addition, Skumlien and colleagues [79] found gender differences regarding effects following a pulmonary rehabilitation program and further research regarding the potential differences in training effects between female and male patients with COPD is required. Therefore, we aim to compare primary and secondary outcome measures for males versus females in pre-specified subgroup analyses to gather information for future studies. Intention-to-treat analysis will be used for all outcome measurements and involve all patients who are randomly assigned. Mixed models will be used to handle missing outcome data. In addition, within the main analysis, an on-treatment analysis will be executed. On-treatment is defined as at least 80% compliance - in other words, at least 20 training sessions or three education sessions depending on group allocation. For data management and statistical analysis the IBM Statistical Package for Social Sciences (SPSS) version 20.0 will be used.

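### The strength ratios behind the elastic-band loads are judged only by a test for Borg differences at P < 0.05, which cannot show that they are right

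*Protocol article*

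**What the plan says.** Secondary outcome 6 in the protocol article is to "Develop a strategy to optimize resistance for each involved movement within an exercise regimen". Under Initial load, step 2, the relative strengths of the six elastic movements are taken from a literature search: "knee extension (100%), chest press (85%), leg curl (65%), elbow flexion (50%), latissimus row (35%), shoulder flexion (30"%). The worked example there treats 10 kg for knee extension and 3 kg for shoulder flexion as the same fraction (55%) of each movement's one-repetition maximum. Under Standardization, each patient's starting band is set from isokinetic shoulder flexion, and the other elastic exercises are scaled from it by the ratios, using fixed distances from the band's insertion.

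The Statistics section then says: "A pre-specified subgroup analysis of participants randomized to the intervention group will be performed", with the purpose "to investigate differences in BORG CR10 rating between elastic resistance exercises to evaluate the strength relationship between involved muscles/movements". The criterion is general: "A difference at the *P* < 0.05 level will be considered significant in all outcome measures and analyses". The section also promises a mean and SD per group with an effect size for each outcome, and 95% confidence intervals and P values for the treatment effect. It states no tolerated Borg difference, and no power is stated for this comparison.

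**The concern.** The ratios are meant to put every elastic movement at the same relative intensity. If they are right, Borg ratings should be about equal across the six exercises, so the conclusion that would support them is one of no relevant difference. The only stated tool is a test for a difference. A significant result can count against a ratio; a non-significant one says little, and it becomes more likely as the sample gets smaller or noisier.

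This comparison is the only one the Statistics section names for checking the ratios. The Progression rule would not reliably correct a wrong ratio: the six elastic exercises move together on ratings in at least three of six, two bands of the same color serve all of them, and the distances are standardized. One mis-scaled movement could therefore persist through the 24 sessions, and an unsupported ratio could be carried into later programs.

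**Working it through.** **Inputs from the protocol.** 22 randomized per group, 17 after the expected 20% drop-out; two-sided 0.05; six elastic exercises, giving 6 × 5 / 2 = 15 pairs.

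**Input not in the protocol.** The SD of the within-patient difference in Borg rating between two exercises (SDd). I assume 1 to 3 points and show the range.

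**The plan's own figure.** The Sample size section uses "a relevant mean difference of 50 meters walked in 6 minutes with a standard deviation (SD) of 52", two-tailed 0.05 and 80% power. n = 2 × (1.960 + 0.842)² × 52² / 50² = 16.98, so 17 per group; 17 / 0.8 = 21.25, so 22. This reproduces. It concerns the 6-minute walk test and says nothing about Borg precision.

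**Chance that a real discrepancy is not significant.** Paired t-test on n patients, one rating per exercise each, noncentrality δ√n / SDd, n − 1 degrees of freedom. For a true difference δ of 1 Borg point:

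| Assumed SDd | 1 | 1.5 | 2 | 2.5 | 3 |
|---|---|---|---|---|---|
| Missed, n = 22 | 1% | 15% | 39% | 57% | 68% |
| Missed, n = 17 | 3% | 27% | 51% | 66% | 75% |

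In SD units, a difference of 0.5 SDd is missed 39% of the time with 22 patients and 51% with 17. 80% power needs a true difference of 0.63 SDd (n = 22) or 0.72 SDd (n = 17). A repeated-measures F-test over six exercises with one exercise off gives similar results: for 1 point at SDd 2, it misses 39% (n = 22) and 53% (n = 17). A true 2-point discrepancy is missed at most 15% (n = 22) or 27% (n = 17) of the time over the same SD range.

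**Effect of averaging sessions.** Take a single-session SDd of 2 (variance 4) and assume that a share f of that variance is session-to-session. Over 20 sessions the variance is 4(1 − f) + 4f/20. For f = 0.3, 0.5 and 0.7, SDd becomes 1.69, 1.45 and 1.16, and the miss rate for 1 point at n = 22 falls from 39% to 25%, 13% and 3%.

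**The opposite error.** If all ratios are right and the 15 pairs are tested unadjusted, the chance of at least one false difference is up to 1 − 0.95^15 = 54%, taking the tests as independent. Pairs that share an exercise are correlated, so the true figure is lower.

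**Precision of an estimate instead.** With equal variances and correlations across exercises, the error variance of one rating is SDd²/2. A patient's deviation from the mean of six exercises then has variance (SDd²/2)(1 − 1/6) = 5SDd²/12, an SD of 0.645 SDd. The 95% half-width is t × 0.645 SDd / √n. At SDd 2 this is 2.080 × 1.29 / √22 = 0.57 points (n = 22) or 2.120 × 1.29 / √17 = 0.66 points (n = 17), before any averaging over sessions. On this scale, one exercise that is 1 point off the other five shows a deviation of 5/6 = 0.83.

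**The case against.** The strongest reply is that the protocol contains no rule that P >= 0.05 confirms the ratios. It says that differences will be investigated and defines when one is significant; a margin or reading rule for a secondary analysis may sit in an analysis plan that is not shown. That stands as far as it goes. A reader might infer that a wrong ratio will often be reported as confirmed, but the document does not say so. What remains is that the one criterion stated cannot deliver what the analysis is for. The risk is also not fanciful: under Initial load, a pilot finding of no significant difference in weight, alongside a strong relationship, is already part of the basis for using the isokinetic peak to set elastic resistance.

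Several limits on size also stand:

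- How frequently an error is missed depends on an SD that the protocol does not give; at SDd 1 a 1-point error is almost always found.
- Ratings are collected after exercises during training, so patients who drop out later still contribute. The 22 figure is the nearer one, and averaging may cut the miss rate a lot.
- A reader might take the ratios to govern every training load. They do not: heel raise and step-up start from body weight, and shoulder flexion is the anchor, so the ratios scale five of the eight exercises.
- The promised mean, SD and effect size may, if they cover these ratings, let readers see the size of differences. They do not supply an interval or a yardstick.
- A margin of 1 point has no source in the documents. With it, a paired equivalence test would have only 47% (n = 22) or 28% (n = 17) power at SDd 2 with a true difference of zero, so inconclusive results are to be expected.

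**Conclusion.** The point holds in a limited form. The stated difference test does not match its purpose: whatever the SD, a non-significant result would not show that the elastic exercises are equally loaded. How much this matters in numbers is uncertain, because the miss-rate ranges rest on the assumed SDd of 1 to 3 points and one rating per patient. The test can err in both directions, so the problem is not a one-way bias toward confirmation. It concerns a secondary, developmental objective within one arm; the primary outcomes and the between-group comparisons are untouched.

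**What to change.** Recast the analysis as estimation. For each elastic exercise, estimate the within-patient difference in Borg rating from the patient's mean over the six exercises, with a mixed model over all sessions and patient as a random effect so that repeated sessions are not counted as independent patients. Report each estimate with a 95% CI. State in advance a tolerated difference, chosen and justified by the investigators on that same deviation-from-mean scale. Call a ratio supported if the interval lies inside it, contradicted if the interval lies wholly outside, and not settled otherwise. Add one sentence saying that P >= 0.05 will not be taken as support for the ratios.

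The cost is a few sentences of analysis text; no new data, visits or patients are needed. The downside is that some ratios will be reported as not settled.

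### The aim is a sex difference in training effect, but the Statistics section plans only a male-versus-female comparison of outcomes and specifies no group-by-gender interaction

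*Protocol article*

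**What the plan says.** The Secondary outcomes section of the protocol article lists as its third item: "Identify if there are any sex-related differences in exercise training effects". The Statistics section returns to the topic, cites earlier findings of gender differences after rehabilitation, and plans: "we aim to compare primary and secondary outcome measures for males versus females in pre-specified subgroup analyses". The sentence ends by giving the purpose as informing later studies. It names no test or estimate for this comparison.

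The same section describes the main model: "In linear mixed models the variable group is considered main, controlling for baseline value, center and gender". It sets one significance rule, under which a difference at P < 0.05 "level will be considered significant in all outcome measures and analyses".

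The Sample size section adds: "The total study group will consist of an equal number of males and females". Randomization is stratified by center and gender. The Discussion says that the trial will add to knowledge of how the sexes respond to exercise training.

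**The concern.** A sex difference in training effect is a difference between two treatment contrasts: intervention minus control in men, against intervention minus control in women. The stated analysis instead compares outcome measures between men and women. The stated model has gender as an additive term, which adjusts the group effect but does not let it vary by sex.

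The wording can be carried out in two natural ways, and neither estimates the target.

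- **A treatment test within each sex, with the verdicts compared.** With 8 or 9 completers per sex per arm, each test is near a coin toss at the planned effect. A result significant in one sex only would then be common even when the effect is the same in both.
- **A direct comparison of men's and women's outcomes.** Any difference between the sexes that exists regardless of training is then counted as a difference in training effect.

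What is at stake is a false statement that the training works in one sex and not the other. Because the comparison is meant to guide later studies, such an error would be carried forward.

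**Working it through.** **Inputs (Sample size section).** 6-minute walk test: "a relevant mean difference of 50 meters walked in 6 minutes with a standard deviation (SD) of 52". Quality of life: "a relevant mean difference of 1 unit (SD 1.07) on the Swedish version of the CRQ". Two-sided alpha 0.05, power 80%, 17 evaluable per arm, 22 recruited per arm, equal numbers of each sex. This gives 17/2 = 8.5 evaluable and 22/2 = 11 recruited per sex per arm.

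**The plan's own figure.** n per arm = 2[SD(1.960 + 0.842)/difference]².
- Walk test: 2(52 × 2.802/50)² = 16.98, so 17, as stated.
- CRQ: 2(1.07 × 2.802/1)² = 17.97, so 18 against the stated 17, a trivial gap.
- Dropout: 17/0.8 = 21.25, so 22, as stated.

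**Reading 1: significance within each sex.** The standard error within one sex is 52 × √(2/n). Power p comes from the noncentral t with 2n − 2 df. With the same true effect in both sexes, the chance that exactly one sex is significant is 2p(1 − p).

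| n per sex per arm | p at 50 m | 2p(1 − p) |
|---|---|---|
| 8 | 0.433 | 49% |
| 8.5 | 0.458 | 50% |
| 9 | 0.483 | 50% |
| 11 | 0.574 | 49% |

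Simulation with 40,000 runs gave 48.7%, 50.1% and 49.0% at 8, 9 and 11. For the CRQ the result is 48% to 50%. An interaction test in the same simulations was significant in 4.9% to 5.1% of runs.

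The figure depends on the true effect. At 8.5 per sex per arm:

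| True effect in both sexes | p | 2p(1 − p) |
|---|---|---|
| 0 m | 0.050 | 9.5% |
| 25 m | 0.153 | 26% |
| 37.5 m | 0.286 | 41% |
| 50 m | 0.458 | 50% |
| 75 m | 0.794 | 33% |

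If baseline adjustment reduced the SD (assumed correlation 0.7, so 52 × √(1 − 0.49) = 37.1 m), p would be 0.737 and 2p(1 − p) would be 39% at 50 m.

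**Reading 2: direct comparison of the sexes.** This was simulated in the intervention arm with 9 per sex, the same training effect in both sexes and no baseline adjustment. The false-positive rate is 5% if the sexes do not otherwise differ. It is 16% if they differ by 25 m regardless of treatment, and 48% if they differ by 50 m. Both gaps are assumptions; the protocol article gives none.

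**What an interaction could show.** The standard error of the difference in effect is 52 × √(4/n), with 4n − 4 df. The difference detectable with 80% power is this standard error times (t0.975 + t0.80).
- n = 8.5 (30 df): SE = 35.7 m; 35.7 × (2.042 + 0.854) = 103 m; power for a 50 m difference 27%.
- n = 11 (40 df): SE = 31.4 m; 31.4 × (2.021 + 0.851) = 90 m; power for a 50 m difference 34%.

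These figures assume no gain from baseline adjustment.

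**The case against.** The strongest reply is that the faulty procedure is inferred. A reader might conclude that the trial will contrast two within-sex P values in place of an interaction, and so produce a spurious sex difference in about half of trials. The protocol article does not support that. It never says that a treatment test will be run in each sex and the two verdicts compared, and it does not rule out an interaction. The additive gender term belongs to the main model for the group effect; the model for the sex comparison is not given. Also, 2p(1 − p) cannot exceed 50%, so the planned effect at this sample size lies close to the worst case. All of this stands, and it is why the figures above are conditional.

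It also stands that the sex comparison is offered as information for future studies, that the sample size does not rest on it, and that the baseline adjustment in the stated model would remove part of a stable sex gap under the second reading.

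Two arguments do not carry. The first is that an article may leave such detail to an analysis plan. This article does state the object compared, the model terms and the significance rule; the problem is that the object compared is not the one in the objective. The second is that an interaction has too little power to be worth naming. Low power is a reason to report an interval and claim little. It is no reason to use a comparison that answers another question, and exploratory results still need the right target.

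**Conclusion.** The point holds in a conditional form. The objective is a difference in training effect between the sexes. The described analysis compares outcomes of males and females, gender is named only as a control variable, and no group-by-gender interaction is specified.

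The consequence depends on how the comparison is carried out. Read from within-sex significance, the false rate reaches about 50% per outcome, given a common true effect of 50 m, SD 52 and about 8 to 11 patients per sex per arm; smaller effects or a useful baseline adjustment lower it. Read as a direct comparison, the error depends on prognostic sex differences that the protocol article does not quantify.

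This concerns a secondary, exploratory objective and leaves the primary comparison untouched. It should be corrected because a wrong conclusion is a real risk and the remedy costs almost nothing.

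**What to change.** For the sex analysis, add a group-by-gender term to the baseline-adjusted mixed model. Report the difference in treatment effect between the sexes with its 95% CI, and make this the only basis for any statement about a sex difference. Give the sex-specific effects from the same model as description only.

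Keep the stated purpose of informing future studies and add one sentence on precision: with 11 down to 8.5 patients per sex per arm, and without gain from baseline adjustment, the difference detectable with 80% power on the walk test is about 90 to 103 m, and power for a 50 m difference is about 34% down to 27%. That sentence also guards against reading a non-significant interaction as evidence that the sexes respond alike.

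The cost is one model term and two or three sentences. Gender is already a stratification factor and a covariate, so no new data or patients are needed.
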